
The ***dietary component*** of the intervention will include 10 (30-min) nutritional counseling sessions with a registered dietitian ([name], RD, PhD). The first 8 counseling sessions will be conducted once/week immediately following a center-based exercise session during months 1-2. The 2 remaining sessions are conducted via biweekly phone during Month 3. The specific dietary objectives of IDEA-P will be consistent with the Therapeutic Lifestyle Changes recommended in the Adult Treatment Panel III Report of the National Cholesterol Education Program (62) and the American Institute of Cancer Research (63). The nutrition intervention encourages reductions in portion size and caloric and fat consumption together with a gradual transition from an animal-based diet to a more plant-rich diet while still incorporating animal foods including milk and meat, with an emphasis on monitoring food proportion and portion size. Specific goals of the dietary component include: (a) reduction in energy intake by 500-1000 kcal per day (for men with a BMI of ≥ 27kg/m2 only; men with a healthy BMI will be instructed to maintain caloric intake); (b) reduction in total fats to 25-30%, saturated fats to 7%, and protein to 15% of total calories; (c) increase in fruit and vegetable consumption to 5 servings per day; (d) intake of 3 or more servings per day of whole grains per day and a gradual increase to at least 25 grams of dietary fiber per day. The nutrition counseling uses a motivational interviewing approach that has been demonstrated to be an effective approach to promote behavior change in cancer patients (64, 65). The nutrition counseling also builds upon many of the cognitive-behavioral self-management strategies utilized in the exercise intervention including self-monitoring, building self-efficacy, goal setting, and anticipating and overcoming barriers to dietary behavior change. Participants will complete 3-day diet records on two different occasions and these records will be used to guide the counseling sessions and to establish nutrition goals. In each of the diet counseling sessions, a dietitian will review the diet records and weight changes and discuss specific ways to meet the diet goals described above. Each visit will consist of establishing specific and tailored dietary goals for the participant to work on and discussing potential barriers to meeting these goals and developing solutions to these barriers. All the exercise and dietary behavioral counseling conducted during intervention and phone contacts is designed to facilitate the development of behavioral self-regulatory skills needed to successfully adopt and maintain change in exercise and dietary behavior. These contacts will specifically address the following content: self-monitoring (recording/tracking exercise and dietary habits), goal setting, barrier problem-solving, and cognitive restructuring (developing more positive attitude/orientation towards behavior change and its associated challenges) using cognitive behavioral and motivational interviewing approaches. Due to the personalized natures of these intervention approaches, the contacts will not be scripted; rather, they will be tailored~~,~~ to the challenges and/or barriers that individual participants are experiencing. An outline of the topics addressed in the exercise and dietary counseling portion of the intervention is provided below:

- *Self-monitoring*: develop awareness and commitment to tracking/recording of desired exercise and dietary behaviors
- *Goal-setting*: Setting short and long-term, process and outcome-related goals for target exercise and dietary behaviors
- *Stimulus Control*: Development of appropriate behavioral, environmental, and reinforcement strategies that help to facilitate adoption and maintenance of change in exercise and dietary habits (e.g., appropriate exercise pacing, providing oneself with exercise and dietary reminders, identifying appropriate rewards for reaching desired exercise and dietary goals, developing healthier grocery shopping/cooking strategies)
- *Barrier problem-solving*: Use of a social problem-solving approach to identify, practice, and implement self and peer-initiated strategies for overcoming common barriers to exercise and dietary behavior.
- *Cognitive restructuring*: Develop a more positive orientation towards exercise and healthy eating (e.g., monitoring affect during exercise to optimize affect/enjoyment, motivational interviewing to identify positive motives and attitudes for changing exercise and dietary behavior).

**Methods for the Standard of Care Intervention Arm (n = 20-25).** Men randomized to the standard of care arm will receive usual PC treatment as well as educational literature describing the American Institute of Cancer Research dietary and physical activity guidelines. To equate contact between treatment arms to levels consistent with similar, contemporary lifestyle intervention trials (32, 38), 20-min phone contacts delivered by [name] clinic staff focusing on routine aspects of PC self-management will be conducted biweekly with men in the standard of care arm. As an incentive to promote retention across the trial, men randomized to standard of care will also receive 2 supervised exercise training sessions and dietary counseling sessions following the completion of the 3 month assessment. Men will complete assessments of all outcomes scheduled at baseline and months 2, and 3.

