This protocol addresses a single-blind, 2-arm randomized controlled pilot study of an intensive lifestyle exercise and dietary intervention in PC patients undergoing prolonged ADT. The primary objective of the Intensive Diet and Exercise Adherence-Pilot (IDEA-P) trial is to determine the feasibility and preliminary efficacy of delivering a combined exercise and dietary counseling intervention to prostate cancer patients undergoing ADT. Preliminary data and effect size estimates obtained from this pilot study will be used as the foundation for the design of larger clinical exercise intervention studies in this priority population of prostate cancer patients. A total of 40 to 50 men undergoing ADT who plan to continue ADT for the next 3 months, will be randomly assigned to receive either the lifestyle exercise and dietary intervention (n=20-25) or standard of care disease management education (n=20-25). Assessment of all functional, anthropometric, and QOL outcomes will be obtained at baseline, after completion of the intervention at 2 months, at a follow-up visit 3 months following the baseline assessment, and at a final follow up visit scheduled between 6 and 8 months following baseline (see Figure 2: Study Design).

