We can recruit men from the clinics of 4 GU medical oncologists, 5 cancer specific urologists, and 1 GU radiotherapist. Information about the study will also be provided to the Columbus Man to Man PC Support group. These recruitment procedures have resulted in successfully reaching target accrual of both minority and total participant levels in several recent PC clinical trials conducted at the OSUCCC and are evidence of the feasibility of successfully recruiting the target sample. Men will be recruited from [name] clinic and the GU Multimodality Clinic where several hundred men previously treated and cured of PC are monitored annually. To further increase the recruitment rate beyond those patients seen in clinic, we will also mail out a letter of introduction to the study to patients on ADT. We will then follow up the mail out of identified patients with a phone call follow-up. Additional recruitment strategies including flyers, newspaper advertisements, and presentations to local PC support groups will also be used. We are optimistic that we can accrue 3-5 men per month at OSU to the trial. As with all lifestyle interventions, we anticipate some attrition, and even a 20% loss to follow-up would result in a sample sufficient to evaluate the primary aims of interest.

**6.2 Inclusion Criteria**.

• *Diagnosed with PC*: histologically-defined diagnosis of PC based upon providing pathology reports and staging studies.

• *Initiating ADT*: will be undergoing a planned course of at least 3 months of ADT. The ADT is defined as: (a) Surgical castration; (b) GNRH antagonist alone; (c) GNRH antagonist with oral androgen receptor blockade, and (d) GNRH antagonist, oral androgen receptor blockade, and 5-alpha reductase inhibitors. We will not include men with only oral antiandrogen therapy such as 5-alpha reductase inhibitors alone or oral antiandrogens alone, as they do not produce castrate levels of testosterone.

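### The closed list defining eligible ADT in Section 6.2 is narrower than the protocol's castrate-testosterone rationale and its stated population of men on ADT

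*Protocol*

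**What the plan says.** Section 6.2 (Inclusion Criteria, the item on initiating ADT) requires a planned ADT course of at least 3 months and then defines the term by four items. The first three are given as "a) Surgical castration; (b) GNRH antagonist alone; (c) GNRH antagonist with oral androgen receptor blockade". The last item in the definition is "d) GNRH antagonist, oral androgen receptor blockade, and 5-alpha reductase inhibitors". Nothing after the fourth item opens the list to equivalents.

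The next sentence gives one exclusion: "We will not include men with only oral antiandrogen therapy such as 5-alpha reductase inhibitors alone or oral antiandrogens alone". It attaches a single reason, which concerns testosterone. Such therapies are left out "as they do not produce castrate levels of testosterone".

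Other sections describe the population more broadly. Section 1 (Study Overview) has "A total of 40 to 50 men undergoing ADT who plan to continue ADT for the next 3 months", and the opening of Section 6 uses the same general description. Section 6.1 (Recruitment) adds "we will also mail out a letter of introduction to the study to patients on ADT". The closing summary of Section 5 says the effect sizes will inform a larger trial in men on ADT. None of these places limits the population by class of drug.

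**The concern.** An inclusion criterion is the rule that screeners apply. Here the rule admits surgical castration and three regimens built on a GnRH antagonist. The reason attached to it concerns castrate testosterone, which is a broader idea than one drug class. A man whose medical regimen is not listed, but who is castrate, fails the definition without falling under the stated exclusion.

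Two things are at stake:

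- **Who the estimates describe.** Section 8 names effect-size estimation for a future application as the primary aim. Objective 2 in Section 3 and the feasibility measures in Section 7 make the recruitment rate an outcome. If the list is applied as written, both describe men on the listed regimens, while the next trial is meant for men on ADT generally.
- **Eligibility deviations.** If screeners follow the broader description instead, men on unlisted regimens enter in breach of Section 6.2.

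**Working it through.** The protocol gives no figure to reproduce on this point. The check sets the text of Section 6.2 against itself and against the population statements.

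**Step 1. Is the list closed?** The wording is definitional, the items run from (a) to (d), and no phrase marks them as examples. Read as written, the list is closed.

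**Step 2. What does each item require?**

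- (a) Surgical castration, with no condition on other therapy.
- (b) A GnRH antagonist, alone.
- (c) A GnRH antagonist and oral androgen receptor blockade.
- (d) A GnRH antagonist, oral androgen receptor blockade and a 5-alpha reductase inhibitor.

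Every non-surgical item therefore requires a GnRH antagonist.

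**Step 3. Test regimens against the list and the exclusion.**

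- *GnRH antagonist plus a 5-alpha reductase inhibitor, no receptor blockade.* It fails (a) because it is not surgical, (b) because the antagonist is not alone, and (c) and (d) because receptor blockade is absent. The 5-alpha reductase inhibitor cannot simply be ignored as a concomitant drug, because (d) counts it as part of the regimen. The exclusion does not apply, because the man is not on oral therapy only. He contains within his regimen a component that (b) accepts by itself, yet he is not eligible. This gap follows from the protocol alone.
- *GnRH agonist, with or without oral agents.* It fails (a) to (d), since none names an agonist. The exclusion does not apply, since this is not oral therapy only. No part of the protocol mentions agonists, either to admit them or to bar them. That agonists are a form of medical castration is general pharmacology and is not stated in the protocol.
- *Surgical castration plus oral receptor blockade.* It meets (a), because (a), unlike (b), does not say alone. There is no gap here.

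**Step 4. Compare with the rationale and the population.** The stated reason for excluding a therapy is failure to reach castrate testosterone. It explains the oral-only exclusion. It does not explain why a medically castrating regimen of another kind should be left out, and no other reason is given. Sections 1, 5 and 6 and the mailing in Section 6.1 all refer to men on ADT without qualification. The men approached and the men to whom results are to be carried forward are therefore a wider group than the men the list admits.

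**Step 5. Can the effect be sized?** That would need the share of otherwise eligible men who are on an unlisted regimen. The protocol does not give it, so the step stops here.

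**The case against.** The strongest reply has four parts.

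- **A definition may be narrower than an overview.** Section 6.2 defines the term that the other sections use, and the castrate-testosterone phrase explains only why oral monotherapy is left out; it is not stated as the test for inclusion. This is fair, and it means that the wording is not a flat contradiction. It remains that the phrase is the only reason given for any boundary, that a restriction to one drug class is nowhere explained, and that the conclusions are planned for the wider group.
- **The agonist example relies on knowledge from outside the protocol.** This is true and should be said. The protocol cannot show whether naming only antagonists is a drafting slip or a choice. The antagonist plus 5-alpha reductase inhibitor example needs no outside knowledge, although nothing suggests that it is common.
- **Little depends on the class of ADT.** It is background therapy, and neither randomisation nor the planned analysis uses it. Recruitment is at one centre, where study clinicians identify candidates and staff confirm eligibility by interview (Section 6.3). This limits the severity but does not repair the rule that those staff must apply.
- **No accrual shortfall is shown.** A reader might infer one by taking the planned rate, "We are optimistic that we can accrue 3-5 men per month at OSU to the trial", and removing men on unlisted regimens. Section 11 has recruitment run from month 4 of Year 1 through month 7 of Year 2, which is 9 + 7 = 16 months, so the planned flow is 16 × 3 = 48 to 16 × 5 = 80 men against a target of 40 to 50. But the rate is stated as accrual to the trial, and Section 11 also calls it target accrual. It already refers to enrolled men, so applying eligibility a second time is not supported, and the share to remove is unknown. This part of the reply stands in full.

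A reader might also infer that surgical castration with oral receptor blockade is left out. Item (a) carries no such limit, so that reading does not hold.

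**Conclusion.** The point holds as a mismatch between an operative eligibility rule and the protocol's own rationale and population. Read literally, Section 6.2 excludes men castrated by a medical regimen that is not on its list. The consequence is one of two, depending on how the rule is applied: a narrower population behind the effect-size and recruitment-rate estimates, or eligibility deviations. It is not both for the same man.

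The conclusion assumes that the list is applied as written and, for the agonist example only, the general pharmacological fact that agonists castrate. It does not assume that the wording is a mistake. The size cannot be computed, because the share of men affected is not given. Severity is moderate: no statistical figure in the plan changes, but the estimates may describe a different group from the one for which they are intended.

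**What to change.** The investigators should reconcile the list in Section 6.2 with its castrate-testosterone rationale and with the population described in Sections 1, 5 and 6. Which way they do so depends on an intention that the protocol does not reveal:

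- **If the list was meant as illustration,** eligible ADT could be defined as surgical or medical castration expected to give castrate testosterone, with the present regimens as examples and the oral-only exclusion kept.
- **If the limit to antagonists is intended,** say so, give the reason, and restrict the target population, the recruitment approach and the planned conclusions to match.

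In either case, record the class of ADT at baseline so that the enrolled group can be described.

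The first route costs one amended sentence and one baseline data item, with no added visits or participants. Its downside is a somewhat more mixed set of ADT regimens, which the recorded class would describe. The second route needs matching edits in the overview, recruitment and summary text, and accepts a narrower claim.

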**6.5 Methods for Both Arms (n = 40-50).** Men expressing an interest in the study will complete a brief screening interview to verify eligibility for inclusion in the trial. Men who meet the inclusion criteria can then sign the consent form during the clinic visit. Participants will complete the Dual-energy X-ray Absorptiometry (iDXA) scan anytime within one month of signing consent. The iDXA will be completed using the high definition GE Lunar iDXA. The iDXA machine is located in the gymnasium of Martha Morehouse, the same building at the Oncology Clinic. All other study visits will be conducted at the Recreation and Physical Activity Center on The Ohio State University main campus. **Please see the appendix for a detailed table of study visits**. At the baseline visit, the study will be explained in greater detail to the participant and all questions will be answered. The baseline visit will be comprised of anthropometric assessments, followed by the functional battery, and exercise and nutrition questionnaire assessments (the questionnaires can be completed at home if preferred by the participant) and finally randomization to either the Exercise and Diet Intervention arm or the Standard of Care arm. Participants will be given the option of completing the questionnaire assessments using the online RedCap data acquisition system. The OSU CCTS Research Informatics Services Core will be used as a central location for data processing and management. Vanderbilt University, with collaboration from a consortium of institutional partners (including OSU) and the NIH National Center for Research Resources, has developed a software toolset and workflow methodology for electronic collection and management of research and clinical trial data. REDCap (Research Electronic Data Capture) data collection projects rely on a thorough study-specific data dictionary defined in an iterative self-documenting process by all members of the research team with planning assistance from the CCTS Research Informatics Services Core. As part of the data dictionary development process, individual fields can be denoted as “identifiers”. When exporting a de-identified dataset, these variables are omitted. Additionally, the data export tool also allows for the shifted of dates for a limited data set export. REDCap provides a secure, web-based application that is flexible enough to be used for a variety of types of research, provides an intuitive interface for users to enter data and has real time validation rules (with automated data type and range checks) at the time of entry. It offers easy data manipulation with audit trails and ad hoc reporting functionality for reporting, monitoring and querying patient records, and an automated export mechanism to common statistical packages (SPSS, SAS, Stata, R/S-Plus). REDCap is 21 CRF Part 11 capable. Currently, REDCap installations support electronic signatures by positively identifying the user through a unique username and password combination. The provisioning of accounts and user access to specific database(s) is integrated with the OSU Medical Center LDAP authentication service, and the provisioning of access and specific user rights are managed by CCTS staff. The use of this technology will streamline subject visits and provide the capacity for precoding research data for export and analysis. Participants will be provided verbal and written instructions on how to wear the objective physical activity monitor (LIFECORDER Plus accelerometer) and will wear it for the next 7-days. Monitors will be returned to trial staff via U.S. postal service. Participants will return for three additional assessment visits: two months after baseline, three months after baseline, and between six and eight months after their baseline visits, and assessments identical to that at baseline will be obtained. Assessment of all functional, anthropometric, and QOL outcomes will be obtained at baseline by project staff who are blinded to participants’ treatment arm assignment.

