**8. Statistical Considerations.**

Significance tests for the efficacy of the lifestyle intervention on the longitudinally gathered data at 2 and 3 months will be individually standardized by baseline values and will be evaluated using a weighted, repeated-measures analysis of variance statistical model adjusting for the effect of age. The primary aim is to estimate effect sizes for a future application. Although the sample size of 40-50 men does not provide optimal statistical power to detect treatment effects, it is feasible sample to recruit given the time and resources provided by the funding mechanism that, while accounting for a 20% attrition rate, would allow for adequate assessment of the feasibility of the intensive lifestyle intervention and obtain the effect size estimates necessary for the design of a large randomized controlled lifestyle intervention trial. Analyses will be conducted using the intention to treat principle with last value carried forward approach used to account for data missing due to participant attrition. Descriptive statistics for the feasibility measures will be calculated prospectively throughout the trial. Exploratory analyses of the direct and indirect pathways of the intervention effects on change in FL and QOL will be conducted using a structural equation modeling longitudinal panel model approach (AMOS 6.0 software; 66, 67). Panel models are ideal for analysis of hypothesized, theory-based relationships across defined periods of time. Again, while the sample size of 40-50 men is not optimal for panel analyses, it is sufficient to obtain estimates of path coefficients necessary to calculate the sample size in order to design an intervention trial that will be appropriately powered to detect meditational pathways of interest.

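### As written, the baseline accelerometer week follows randomisation, and home or online questionnaires and the diet record may do so too, so effect estimates for these measures can be biased

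*Protocol*

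**What the plan says.** Protocol section 6.5 (Methods for Both Arms) gives the order of the baseline visit: "The baseline visit will be comprised of anthropometric assessments, followed by the functional battery, and exercise and nutrition questionnaire assessments". The sentence continues with the home option and ends in allocation: "the questionnaires can be completed at home if preferred by the participant) and finally randomization to either the Exercise and Diet Intervention arm". An online route is also open: "Participants will be given the option of completing the questionnaire assessments using the online RedCap data acquisition system". Neither route has a return date or a condition that forms be in before allocation.

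The same section then turns to the activity monitor. After instruction, the man "will wear it for the next 7-days", and "Monitors will be returned to trial staff via U.S. postal service".

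The baseline iDXA may be done "anytime within one month of signing consent". Both schedules in the Appendix, however, mark the first scan in the oncology clinic column, ahead of the column for baseline and randomisation. The schedules also mark a three-day diet record at baseline. They have no row for the accelerometer.

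Section 8 says that the 2- and 3-month data "will be individually standardized by baseline values" before the efficacy tests, and that the primary aim is to estimate effect sizes for a later application.

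**The concern.** A baseline value is useful for standardising follow-up because randomisation makes it independent of treatment. A value recorded after the man knows his arm has lost that property. The trial is single-blind: the staff who assess at baseline are blinded, but the men are not, and blinded assessors cannot protect what a man reports or does in the week after he learns his arm.

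Any between-arm difference already present in such a baseline is carried into the standardised outcome. The pilot exists to supply effect sizes for a definitive trial, so a biased estimate passes straight into that trial's sample size. A pre-allocation baseline that was never collected cannot be recovered later.

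**Working it through.** The protocol gives no figure to reproduce on this point, so the check is mainly one of sequence.

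**Step 1: where each baseline measure falls relative to randomisation.**

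| Measure | What the protocol fixes | After allocation? |
|---|---|---|
| Timed tasks, strength, weight, Bod Pod | Functional and anthropometric batteries, first in the visit (6.5, 7) | No |
| Mobility self-efficacy | Completed with the functional tests (7) | No |
| LL-FDI | Listed in the functional battery (7) | No, on the face of the text |
| Accelerometer | Seven days following the visit, returned by post (6.5) | Yes, every man |
| Exercise and nutrition questionnaires | Home or online, no deadline (6.5) | Permitted |
| QOL, pain, fatigue, exercise self-efficacy scales | Covered only if the home or online option extends to all questionnaires | Possible, by inference |
| Three-day diet record | Marked at baseline; cannot be completed within one visit; no earlier issue stated (Appendix) | Possible |
| iDXA | Window tied to consent (6.5); before randomisation (Appendix) | Text allows it, Appendix does not |

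**Step 2: accelerometer, illustration.** Let B be activity before the study, T the true gain at follow-up and c the session activity recorded in the wear week. Reading the standardisation as a change from baseline (an assumption):

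measured change = (B + T) − (B + c) = T − c.

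The intervention arm has two supervised one-hour sessions in Week 1, each with 10–30 minutes of aerobic work (section 6.5). So:

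- wear week ends before Week 1: c = 0 from sessions;
- both sessions inside the wear week, aerobic part only: c = 2 × 10 = 20 to 2 × 30 = 60 minutes;
- both sessions inside, whole hour counted (upper bound): c = 2 × 60 = 120 minutes.

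If aerobic time rises from 10 to 30 minutes per session by follow-up, T = 60, c = 20 and the measured gain is 40 minutes, a loss of one third. If the follow-up sessions equal those in the wear week, T = c and the measured gain is zero.

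**Step 3: questionnaires, illustration.** Let h be the share of men who complete forms after allocation and δ the between-arm shift, in SD, that knowledge of the arm causes at baseline. A change-based effect is then biased by about −h × δ. With h = 0.5 and δ = 0.2 to 0.4 (both assumed), the bias is 0.5 × 0.2 = 0.10 to 0.5 × 0.4 = 0.20 SD. If δ is positive (intervention men report better at once), the effect is understated; if negative, it is overstated.

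**Step 4: what that does to the next trial.** Per arm, n = 2(1.960 + 0.842)² / d² ≈ 15.70 / d² (two-sided 0.05 and 80% power, assumed). Starting from an assumed true d = 0.5:

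| Estimated d | n per arm |
|---|---|
| 0.5 (no bias) | 15.70/0.25 → 63 |
| 0.4 (understated by 0.10) | 15.70/0.16 → 99 |
| 0.3 (understated by 0.20) | 15.70/0.09 → 175 |
| 0.6 (overstated by 0.10) | 15.70/0.36 → 44 |
| 0.7 (overstated by 0.20) | 15.70/0.49 → 33 |

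The inputs to Steps 3 and 4 are illustrative, not document values.

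**The case against.** The strongest reply is that the main outcomes are protected. A reader might infer that every efficacy test rests on a contaminated baseline. The documents do not support this: the functional and anthropometric batteries come before randomisation, and these hold the timed tasks, strength, weight and Bod Pod. That part of the objection stands. Accelerometry, the one measure that always falls late, is listed in section 7 among the behavioural and feasibility measures; it is not one of the functional, body composition or QOL outcomes of Objective 1. That stands too.

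A reader might also infer that the iDXA is planned after randomisation. It is not. The text window is loose, but the Appendix puts the scan first, and section 6.5 refers the reader to the Appendix for the visit schedule. This is a discrepancy to reconcile.

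The home option is attached to the exercise and nutrition forms, and section 6.5 says that QOL is obtained at baseline by blinded staff. Extending the option to the QOL, pain, fatigue and exercise self-efficacy scales is an inference, supported only by the general wording of the online option. Permitting home completion is also not the same as planning it after allocation.

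Overlap of the wear week with Week 1 is likewise not stated. Counselling in groups of 3–5 with accrual of 3–5 men a month would be compatible with a gap before Week 1. A gap would remove the session effect from the wear week, but not the man's knowledge of his arm.

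**Conclusion.** The point holds for a limited set of measures. Followed as written, section 6.5 places the baseline activity week after randomisation for every man, and it allows the exercise and nutrition questionnaires to be completed after allocation. The diet record and, by inference, the other self-report scales may share the problem. Because section 8 standardises by baseline, effect estimates for these measures can be biased in either direction by knowledge of the arm and, if Week 1 starts within the wear week, by the intervention.

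The size is unknown. It depends on how many men complete forms late, how far allocation shifts their answers, when Week 1 starts, and how the standardisation is defined. The figures above show only that modest shifts would matter for planning. The timed tasks, strength, weight and Bod Pod are unaffected. The case for change is that the remedy is cheap and the lost baselines cannot be recovered. It is not that the trial's main comparisons are invalid.

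**What to change.** Use the interval that already exists. Section 6.3 has a telephone call after consent that confirms eligibility and schedules the baseline visit. After that call, issue the accelerometer, the questionnaires or REDCap link, and the diet record, and have the man bring or submit them by the baseline visit.

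Add one sentence to section 6.5: allocation is made and revealed only once the accelerometer week, questionnaires, diet record and baseline iDXA are complete. This also brings the iDXA text into line with the Appendix. Add an accelerometer row to both schedules.

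If a baseline value is still obtained after allocation, keep it, flag it with its date and examine its influence in a sensitivity analysis. Setting such values to missing would waste data in a trial of 40–50 men.

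The cost is about one week before randomisation and some added scheduling to get monitors and forms out after the eligibility call. No new visit or assessment is needed.
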